#### Randomization and Blinding

In this open-label intervention study, participants will be centrally randomized at a 1:1 allocation ratio into intervention and control groups using the stratified permuted-block randomization methods based on the following stratification variables:

Institutions (1–15 institutions).Age at enrollment (70–77 years vs. 78–85 years).Glycemic control relative to the glycemic targets recommended by the JDS/JGS joint committee (optimally controlled vs. poorly or excessively controlled).Drugs potentially associated with severe hypoglycemia such as insulin, sulfonylureas and glinides (those receiving these drugs vs. those not receiving these drugs).

The randomization sequences will be generated by a trial statistician ([name]) by using Proc Plan in SAS version 9.4 (SAS Institute, Cary, NC, USA). Study participants and research staff including investigators and clinicians at each institution will be unaware of the randomization sequences and block size. Research staff responsible for primary outcome data collection will also be blinded to group assignment, to which, however, the intervening research staff and the participants will be not blinded.

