## Methods and Materials

### Study Design and Setting

The J-MIND-Diabetes study was designed as a 18-month, open-labeled, randomized, controlled, multicenter trial of multi-domain intervention targeting modifiable risk factors for dementia among T2DM patients with cognitive impairment. To be organized by a central coordinating center at the National Center for Geriatrics and Gerontology (NCGG), this study involves 16 centers located in Japan. This study will randomize 300 T2DM patients with cognitive impairment into intervention or control groups. The multi-domain intervention will address the following 4 domains: (1) management of metabolic and vascular risk factors (diabetes, hypertension, and dyslipidemia); (2) physical exercise and self-monitoring of physical activity; (3) nutritional guidance; and (4) promoting social participation. The control group will receive usual diabetes care and general instructions on dementia prevention. The primary and secondary outcomes will be assessed at baseline, 6, and 18 months in both groups (see the study flow diagram shown in Figure 1).

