### Statistical Considerations

#### Sample Size

Using the open source sample size calculator (http://www.openepi.com/SampleSize/SSMean.htm), the sample size was calculated based on preliminary data from MMSE assessments over 1-year (1.03 ± 0.36 years) in 83 patients with MCI and T2DM classified into category II among the Memory Clinic at the NCGG, since no multi-domain intervention trials have been conducted to date in this population. The mean change in MMSE score among 83 patients was −1.45 ± 3.55. Of these, the optimally controlled group (n = 30) showed a mean change in MMSE score of −0.33 ± 2.58. Based on these preliminary data, it was hypothesized that the present study is likely to detect differences in change of cognitive function between the intervention and control groups (intervention group vs. control group, −0.33 ± 2.58 vs. −1.45 ± 3.55). With a two-sided significance level of 5% and a statistical power of 80%, the total sample size required for the unpaired *t*-test was calculated as 242. In addition, dropout rates at final follow-up is estimated to be 15–20% at each institution, thus a total of 300 patients are required.

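### Four stratification factors make 120–128 strata for 300 patients, so blocking gives only partial balance; the primary model should adjust for them, and 15 institutions must be reconciled with 16 centres

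*Protocol article*

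**What the plan says.** Under Randomization and Blinding, the protocol article states that "participants will be centrally randomized at a 1:1 allocation ratio", "using the stratified permuted-block randomization methods based on the following stratification variables". Four variables follow:

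- institution: "Institutions (1–15 institutions";
- age: "Age at enrollment (70–77 years vs. 78–85 years";
- glycaemic control against the recommended targets: "optimally controlled vs. poorly or excessively controlled";
- drugs linked to severe hypoglycaemia: "those receiving these drugs vs. those not receiving these drugs".

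No block size is given; it is withheld from site staff. Study Design and Setting says that "this study involves 16 centers located in Japan", and nothing explains why the stratification list has 15. Sample Size concludes "thus a total of 300 patients are required". Under Data Analyses, the terms of the primary MMRM are group, visit, group-by-visit interaction and baseline composite score. No stratification variable is among them.

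**The concern.** Permuted blocks force balance only when blocks are completed. With about as many strata as there are groups of two or three patients, many strata end inside a block, and the balance sought on four factors is only partly obtained. That matters most for glycaemic control, because the sample-size section itself treats it as related to cognitive decline. Whatever imbalance remains is then left in the treatment comparison, because the stated primary model adjusts for none of the four factors. The same omission discards precision even where balance was achieved, because the unadjusted standard error does not credit the stratification.

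Separately, the institution factor has one level fewer than the number of centres. Its levels define the allocation lists, so the two counts must agree or the difference must be explained.

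**Working it through.** **1. The plan's own figure.** Sample Size gives mean MMSE changes of −0.33 (SD 2.58) and −1.45 (SD 3.55), two-sided 5% and 80% power.
Per arm: (1.96 + 0.84)² × (2.58² + 3.55²) / 1.12² = 7.85 × 19.26 / 1.254 ≈ 121, so 242 in total, as stated. Allowing for dropout, 242/0.85 = 285 and 242/0.80 = 303, so 300 is reasonable.

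**2. Strata.**
- 15 × 2 × 2 × 2 = 120 strata; 300/120 = 2.5 patients each.
- 16 × 2 × 2 × 2 = 128 strata; 300/128 = 2.34 patients each.

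**3. What blocking then achieves.** This was simulated with 300 patients, 15 or 16 sites, and equal or uneven site sizes and factor splits (1,500 trials per scenario). Block sizes, site sizes and factor splits are assumptions, because the article does not give them.

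| Scheme | Opened blocks left unfinished | Mean arm difference in a binary factor (percentage points) | 95th percentile | Arm-size difference: mean (95th percentile) |
|---|---|---|---|---|
| Blocks of 2 | 30–35% | 1.9–2.1 | about 5 | 6–7 (14–16) |
| Blocks of 4 | 66–79% | 2.5–2.9 | 6–7 | 7–8 (18–20) |
| Blocks of 6 | 84–97% | 2.9–3.5 | 7–9 | 9–10 (22–24) |
| Simple randomisation | n/a | 4.4–4.8 | about 11 | 14 (34) |

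A re-run with equal sites and 36% optimally controlled (30/83, the pilot share) gave mean differences in glycaemic control of about 2.2, 2.9 and 3.5 points for blocks of 2, 4 and 6, against 4.5 with simple randomisation.

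**4. What the imbalance could do.** In the pilot, 83 patients averaged −1.45 and the 30 optimally controlled averaged −0.33. The other 53 therefore averaged (83 × −1.45 − 30 × −0.33)/53 = −110.45/53 = −2.08. The gap is 2.08 − 0.33 = 1.75 MMSE points.
- Mean imbalance, 2–3.5 points: shift of 0.02 × 1.75 = 0.04 to 0.035 × 1.75 = 0.06.
- 95th percentile, 5–9 points: shift of 0.05 × 1.75 = 0.09 to 0.09 × 1.75 = 0.16, which is 8–14% of the planned difference of 1.12.
- Standard error of the contrast with 121 per arm: √(19.26/121) = 0.40.

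**5. What adjustment could recover.** On the pilot figures, glycaemic control accounts for 0.361 × 0.639 × 1.75² = 0.71 of a total variance of 3.55² = 12.60, or about 6%. This is on the MMSE scale and before adjusting for baseline score.

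**The case against.** The strongest reply is that the design still works. Blocking within these strata cuts imbalance by roughly 25–60% against simple randomisation at every block size tried. Remainders in different strata have independent signs and largely cancel. Chance imbalance is already covered by the significance level, and a typical shift of 0.04–0.06 MMSE points is small beside a standard error of 0.40. All of that stands.

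Four stronger readings are tempting, and the documents do not support them.

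- **The four factors end up unbalanced.** They do not. Balance is weakened, not lost.
- **Most blocks are left unfinished.** This holds for blocks of 4 or 6, but the block size is not given, and with blocks of 2 only about a third are unfinished.
- **One centre has no randomisation list.** The text shows only two different counts. A non-enrolling coordinating centre would explain them.
- **Site brings rater effects into the result.** No such effect is documented. Psychologists were trained centrally, the complex-figure test is scored by one psychologist, those collecting the primary outcome are blinded, and the outcome is a change from baseline.

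Nor is a change of allocation method clearly better. Blocking only on institution and glycaemic control (blocks of 4) improves balance on glycaemic control, but worsens the mean age difference from 2.7 to 4.5 points. Minimisation gives tighter balance, but a switch during recruitment produces a mixed allocation scheme, and the article does not say how many patients remain to be randomised.

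A separate analysis plan may also add the stratification factors. The article, however, states the model's terms, and they are not among them.

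**Conclusion.** The concern holds in a limited form. The count of 120–128 strata, at 2.3–2.5 patients each, is arithmetic from the protocol. The conflict between 15 institutions and 16 centres is plain on the page and unexplained. The size of the residual imbalance (about 2–3.5 points on a binary factor on average, and arm sizes differing by about 14–24 patients at the 95th percentile) depends on assumed block sizes, site sizes and factor splits.

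The consequence is chance imbalance and some lost precision; the comparison remains valid and unbiased. The direct power loss from a 160:140 split is under 1%. The prognostic gap of 1.75 MMSE points comes from 83 patients in an observational pilot, and on one component of the composite. It is also taken that optimally controlled means the same in the pilot as in the randomisation. What is fixed badly is the primary model, which omits the factors on which allocation is restricted when including them would cost almost nothing.

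**What to change.** 1. Add age group, glycaemic control and hypoglycaemia-risk drug use to the primary MMRM as fixed effects, and institution as a fixed or random effect. Do this before unblinded data are analysed. The cost is a short amendment to the analysis section and, with institution fixed, 17 or 18 extra parameters in all (3 for the binary factors plus 14 or 15 for institution). No new data are needed, since every factor is recorded at randomisation.
2. Reconcile 15 institutions with 16 centres: correct whichever count is wrong, or state why one centre is not a level of the factor, and confirm that every enrolling centre is in the allocation system. The cost is one check and one sentence.
3. Optional: if substantial recruitment remains, the sponsor may weigh fewer strata or minimisation with a random element, since allocation is already central. This would mean reprogramming, an amendment and a mixed allocation scheme, and is not a required change.

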#### Data Collection Forms and Data Monitoring

All measurements will be assessed by trained personnel. Most outcome measurements will be collected using papers forms at each institution. Then, these data will be collected through entry of these data by assessors using electronic data capture (EDC) systems. Paper forms will be retained as back-ups at each institution as required.

On-site monitoring will be conducted at each institution to ensure that the patient rights are protected, the reported data are accurate, and the conduct of the trial is compliant with the current approved protocol. The monitor will ensure that (1) written informed consent is obtained from all participants before their participation in this trial; (2) primary outcome data reported in the EDC are complete and accurate; and (3) all adverse events and serious adverse events are reported appropriately.

#### Data Analyses

Data will be presented as means, medians, standard deviations, ranges and interquartile ranges for continuous and ordinal variables, and counts and percentages for categorical variables. Differences in baseline clinical characteristics between the intervention and control groups will be examined for significance by using the *t*-test or the Mann-Whitney U test for continuous variables and by the chi-squared test or the Fisher's exact test for categorical variables, as appropriate.

To evaluate differences in cognitive changes from baseline at 18-month follow-up between the intervention and control groups, the mixed-effects model for repeated measures (MMRM) with an unstructured covariance structure will be conducted using groups, time of the visit, group by time interaction, and baseline composite cognitive score as covariates. For the secondary continuous variables, the same analyses using MMRM will be performed. For the secondary categorical variables, logistic regression analyses or chi-squared tests will be conducted as appropriate. Frequencies of adverse events and serious adverse events will be summarized and compared between the intervention and control groups by using the chi-squared test or the Fisher's exact test.

All statistical analyses will be performed using SAS 9.4 (SAS Institute, Cary, NC, USA). *P*-values <0.05 will be considered statistically significant.

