##### Physical Exercise and Self-Monitoring of Physical Activity

All participants will engage at least twice a month in a physical exercise program provided at participating institutions by study physiotherapists or trained instructors, which consists of aerobic exercise, muscle strength training, postural balance retraining, and dual-task training, namely “cognicise” (“cogni” for cognition + “cise” for exercise), involving physical and cognitive tasks. The combined activity program intervention including cognicise was shown to improve cognitive and physical performance in older adults with MCI (Shimada et al., 2018). This program will be composed of a 5-min medical check (blood pressure, pulse rate), a 15- to 20-min training including stretching, muscle strength exercise and postural balance training, a 5-min rest, a 20- to 30-min aerobic exercise, a 5-min rest, and a 20- to 30-min dual-task training. The aerobic exercises, including stair stepping and endurance walking will be performed with the mean aerobic exercise intensity set as moderate intensity according to the Karvonen formula: Target heart rate [HR] = [40–60% × (maximum HR – resting HR)] + resting HR. The maximum HR will be estimated for each participant by using the age-predicted maximal HR formula (220 – age). All participants will be assessed for HR immediately after an aerobic exercise based on their pulse rates. The participants will also be recommended to conduct daily home-based muscle-strengthening exercises, walking, and dual-task training at least twice a week, as well as to self-monitor these activities using study-provided booklets and pedometers.

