##### Social Participation

To promote social participation, participants will be requested to go out at least three times a week. Moreover, participants will be requested to monitor their social activities including taking care their grand-children, doing work/volunteer work, face-to-face conversation, shopping/eating-out, and participating in organizations or groups by using a study-provided booklet every day. Again, to encourage an active lifestyle, a meeting will be heled after each physical exercise session, where participants discuss their physical, social, and cognitive activities among themselves.

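### The primary MMRM leaves out both institution and any clustering from shared exercise sessions in the intervention arm, so its standard error may be wrong in either direction

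*Protocol article*

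**What the plan says.** The Data Analyses section names the primary model for the 18-month contrast: "the mixed-effects model for repeated measures (MMRM) with an unstructured covariance structure will be conducted using groups, time of the visit", followed by the group-by-time interaction and the baseline composite score. Correlation is modelled within a patient only. No institution, instructor or exercise-group term is listed.

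The Randomization and Blinding section says "participants will be centrally randomized at a 1:1 allocation ratio into intervention and control groups using the stratified permuted-block randomization methods". The strata are institution, age, glycemic control and use of drugs that can cause severe hypoglycemia. None of them is in the listed model.

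In the intervention arm, patients attend at least twice a month a "physical exercise program provided at participating institutions by study physiotherapists or trained instructors". Under Social Participation, "a meeting will be heled after each physical exercise session, where participants discuss their physical, social, and cognitive activities among themselves". The Control Group section describes usual care plus general instructions at baseline, with no group sessions.

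The article does not give an intraclass correlation, the number of exercise groups per institution, or their size.

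**The concern.** Two sources of correlation between patients are left out of the stated model.

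The first arises after randomization and in one arm only. Intervention patients at an institution share instructors, sessions and a discussion meeting for up to 18 months. If groups differ in how well they work, those patients' outcomes are correlated and the intervention mean varies more than the model assumes. Randomizing individuals does not remove correlation created by delivery.

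The second is institution itself. Differences between institutions that affect both arms alike largely cancel from the treatment contrast, because allocation is balanced within institution. With institution left out of the model, they stay in the residual and widen the standard error.

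At stake is the accuracy of the confidence interval and p-value for the single primary contrast, which is judged at P<0.05 in a trial sized at 80% power with no allowance for clustering.

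**Working it through.** **1. The plan's own figure.** The Sample Size section uses "intervention group vs. control group, −0.33 ± 2.58 vs. −1.45 ± 3.55", two-sided 5% and 80% power:

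n per arm = (2.58² + 3.55²)(1.960 + 0.842)² / 1.12² = 120.5, so 121 per arm and 242 in total.

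This reproduces the stated result ("the total sample size required for the unpaired *t*-test was calculated as 242"). It treats all patients as independent.

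**2. Patients per institution.** The article says "dropout rates at final follow-up is estimated to be 15–20% at each institution, thus a total of 300 patients are required". That leaves 300 × 0.80 = 240 to 300 × 0.85 = 255 completers, or about 120 per arm at the lower end. The stratification list gives 15 institutions and Study Design and Setting gives 16, so m = 120/15 = 8.0 or 120/16 = 7.5 intervention patients each. Treating each institution as one exercise group is an assumption.

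**3. Exercise-group effect only.** Assume an intervention-arm intraclass correlation (ICC) of 0.01–0.05, m = 8 and equal arm variances.

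- Design effect in that arm: DE = 1 + (m − 1) × ICC
- Variance ratio of the contrast, true to model: R = (1 + DE)/2
- Actual type I error: 2[1 − Φ(1.96/√R)]
- Power with a correct standard error: Φ((1.960 + 0.842)/√R − 1.960)

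| ICC | DE | R | Type I error | Power |
|---|---|---|---|---|
| 0.01 | 1.07 | 1.035 | 5.4% | 79% |
| 0.02 | 1.14 | 1.070 | 5.8% | 77% |
| 0.05 | 1.35 | 1.175 | 7.1% | 73% |

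**4. Adding an institution effect common to both arms.** Set the intervention-arm variance to 1. Let rg be the share from the exercise group and rb the share from an institution effect common to both arms. For the listed model, which omits both:

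R = [m·rg + 2(1 − rb − rg)] / [2rb + 2(1 − rb − rg) + rg]

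Type I error at 15 institutions, m = 8:

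| rg | rb = 0 | rb = 0.05 | rb = 0.10 |
|---|---|---|---|
| 0 | 5.0% | 4.4% | 3.9% |
| 0.01 | 5.4% | 4.8% | 4.3% |
| 0.02 | 5.8% | 5.2% | 4.7% |
| 0.05 | 7.1% | 6.5% | 5.9% |

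The error exceeds 5% only when rg > 2rb/(m − 1), which is 0.29·rb at m = 8 and 0.31·rb at m = 7.5. Simulation of a two-group comparison at a single visit agrees with the table.

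**5. Adjusting for institution alone.** In simulation (15 institutions, 8 patients per arm in each, single visit), adding a common institution factor and nothing else gives about 5.4–5.7%, 5.7–5.9% and 7.2–7.4% for rg = 0.01, 0.02 and 0.05. The common institution effect hardly changes these figures, because the adjustment takes it out of the residual and so removes the offset.

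**6. An intervention-only random institution effect without a common institution term.** The random term then absorbs variance that both arms share and that cancels from the contrast. Simulated error falls to about 1.8–3.1% when rb is 0.05–0.10. Neither term is adequate alone.

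**The case against.** A reader might infer that the standard error is certainly too small and the true error certainly above 5%. The documents do not support that. No ICC is given, and if sessions create no shared variation, the listed model keeps the error at or below 5%. The omitted institution stratum also pushes the other way, as step 4 shows. This objection stands, and the point is worded accordingly.

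The size can also be challenged, and these challenges stand as limits on it:

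- Figures of 7.7% and 72% result at ICC 0.05 only with 10 patients per institution, which means no dropout.
- The only standard deviations given, for MMSE change, put 2.58²/(2.58² + 3.55²) = 35% of the contrast variance in the intervention arm rather than half. With those, m = 8 gives about 5.3–6.4% error and 75–79% power. The composite's standard deviations are not given.
- Nutritional counselling is individual, and home exercise, self-monitoring and risk-factor treatment are not described as group activities. A small ICC is therefore plausible, and at 0.01–0.02 the excess is under one percentage point.

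Finally, this is a condensed article, and an analysis plan that is not shown may add terms or sensitivity analyses. That is a fair caution. But the article does not leave the primary model open: it lists the terms, and the list omits a stratification factor and the clustering that the described delivery could create. Nor is it an answer that the two omissions may offset each other. The balance is accidental, and the usual repair of adding institution removes it.

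**Conclusion.** The point holds in conditional form. The listed primary model treats patients as independent of one another, although institution is a stratification factor and intervention patients alone share sessions and meetings there. Its standard error may therefore be too small or too large.

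With an assumed intervention-arm ICC of 0.01–0.05, 8 evaluable patients per institution, equal arm variances and no common institution effect, type I error is about 5.4–7.1% and power about 73–79%. A common institution share of 0.05–0.10 lowers the listed model's error to about 4.3–6.5%. Adjusting for institution alone gives about 5.4–7.4%. The ICC, the common institution share and one exercise group per institution are all assumptions, and the calculations treat a single visit rather than the full repeated-measures model. The distortion is modest, but it affects the one test on which the primary claim rests and is cheap to address.

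**What to change.** Add institution and the other three stratification factors to the primary MMRM.

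Prespecify, as a sensitivity analysis for the 18-month contrast, the same model plus a random institution effect that applies only in the intervention arm. If an institution runs several exercise groups, use an exercise-group effect instead. Use Kenward-Roger degrees of freedom and report the estimated intraclass correlation. Keep the common institution term in this model, for the reason in step 6.

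The cost is analysis wording and one extra variance term in software already planned. No additional patients or outcome measurements are needed, though exercise-group membership must be on record if institutions run more than one group. The downside is a slightly wider, somewhat conservative interval and a variance component estimated imprecisely from 15–16 institutions. That imprecision is a reason to make the clustered model a sensitivity analysis rather than the primary one.

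### The primary MMRM omits all four randomisation stratification factors, which forgoes a small gain in precision but does not threaten validity or the planned power

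*Protocol article*

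**What the plan says.** Under Randomization and Blinding, participants are "centrally randomized at a 1:1 allocation ratio into intervention and control groups using the stratified permuted-block randomization methods". Four factors define the strata:

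- institution, with 15 levels
- age group: "Age at enrollment (70–77 years vs. 78–85 years")
- glycaemic control against the recommended targets: "optimally controlled vs. poorly or excessively controlled"
- drugs linked to severe hypoglycaemia: "those receiving these drugs vs. those not receiving these drugs"

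Under Data Analyses, the primary comparison at 18 months is an MMRM with unstructured covariance, fitted "using groups, time of the visit, group by time interaction, and baseline composite cognitive score as covariates". The same kind of model is carried over to the continuous secondary outcomes. No stratification factor is in the list, and no other section adds one or gives a reason for leaving them out.

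Under Sample Size, the trial is sized for an unpaired t-test, so with no covariate adjustment at all.

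**The concern.** Stratified allocation makes the arms more alike on the stratification factors than simple randomisation would. If those factors predict the outcome, the true variance of the treatment difference falls. A model without them leaves their contribution in the residual, so its standard error does not reflect that fall and the test becomes conservative. Where blocks stay incomplete and some imbalance remains, the model does not correct for it either. In both cases precision is lost that could have been had from data recorded at randomisation.

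The Sample Size section itself points to one omitted factor as prognostic. It takes the hypothesised intervention-group change from the optimally controlled patients in the preliminary cohort, and glycaemic control is then used as a stratification factor but not as a covariate.

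**Working it through.** **1. Reproduce the plan's sample size.** Inputs from Sample Size: changes of −0.33 (SD 2.58) and −1.45 (SD 3.55), two-sided 5%, power 80%.

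- Difference = 1.12. Common SD = √((2.58² + 3.55²)/2) = 3.103.
- n per arm = 2 × (1.960 + 0.842)² × 3.103² / 1.12² ≈ 120.5, so 121 per arm and 242 in total, as stated.
- Inflating for dropout gives 242/0.85 = 285 and 242/0.80 = 303, so 300 is in line.

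**2. How prognostic is glycaemic control on the plan's own figures?** All 83 preliminary patients changed by −1.45 (SD 3.55), and the 30 optimally controlled by −0.33. The other 53 are taken to be not optimally controlled.

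- Mean of the 53 = (83 × −1.45 − 30 × −0.33)/53 = −2.08, a difference of 1.75 from the 30.
- Between-group sum of squares = 30 × 1.12² + 53 × 0.634² ≈ 58.9. Total = 82 × 3.55² ≈ 1033.4.
- R² ≈ 58.9/1033.4 = 0.057. Adjusted R² is 0.045, and an approximate Fisher-z 95% interval for R² runs from about 0.001 to 0.19.

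**3. Upper-end formula.** If adjustment removed all of this variance at no cost, the residual SD would shrink by √(1 − 0.057). The unadjusted standard error would then be 1/√0.943 = 1.03 times the adjusted one. Power with 242 evaluable patients would go from 80.2% to 82.4%, or N for 80% power from 242 to 228.

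**4. Allow for partial balance.** 15 × 2 × 2 × 2 = 120 strata for 300 patients is 2.5 per stratum. With the 16 centres named under Study Design and Setting it would be 128 strata and 2.3. Many blocks will stay incomplete, so the formula needs checking by simulation.

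Settings: 300 patients, 15 sites, 20% random dropout, effect 1.12/3.103 = 0.36 SD, 36% optimally controlled (30/83), linear model at one endpoint, 6,000 trials per scenario. Assumed because the article does not give them: blocks of 4, sites of equal expected size, and even splits on age and drug use. The further 6% is divided equally between age and site.

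| Variance explained | Model | Mean SE | Power |
|---|---|---|---|
| Glycaemic control 5.6% only | Unadjusted | 0.129 | 79.8% |
| | + three binary factors | 0.126 | 81.1% |
| | + site as fixed effect | 0.128 | 80.7% |
| Plus 6% from age and site | Unadjusted | 0.129 | 80.4% |
| | + three binary factors | 0.124 | 83.2% |
| | + site as fixed effect | 0.124 | 83.0% |

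Monte Carlo error on a single power figure is about √(0.8 × 0.2/6000) = 0.5 points. The three models were fitted to the same trials, so differences between them are better determined than that.

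**5. Type I error.** With glycaemic control as the only prognostic factor, the unadjusted test rejected in 5.0% of null trials, so the conservatism is not visible. With the further 6%, the unadjusted mean SE was 0.129 against an actual SD of 0.125 and the size was 4.1%. With all four factors in the model the size was 4.9%.

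**6. If no factor is prognostic.** Adjustment then gains nothing, and fitting all sites as fixed effects (14 terms) costs about 1 to 2 points of power.

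**The case against.** The strongest reply is that nothing is invalid. The estimate is unbiased, the test does not reject too often, and the planned 80% power assumed an unadjusted t-test. The MMRM already adjusts for the baseline composite, which the sizing did not credit. All of this stands. A reader might infer that the trial is underpowered or its primary p-value unreliable; the documents do not support that.

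Second, the evidence that the factors matter is thin. A reader might infer from the Sample Size section that glycaemic control is strongly related to cognitive change. An R² of 0.057 from 83 patients, with an interval reaching almost to zero, does not show that. It also describes MMSE change over about a year without baseline adjustment, whereas the primary outcome is an 18-month multi-test composite given baseline. For institution, the Assessment section describes central training of psychologists and single-rater scoring of the complex figure test, and a constant site shift largely cancels in change from baseline. This stands, and it limits the size of the point.

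Third, larger figures are easy to produce. With an assumed R² of 10–15% and free, complete adjustment, the formula gives 84–86% power. With complete balance and R² between 5.7% and 15%, it gives a true size of 4.4% down to 3.4%. These should not be used as the magnitude: the R² values above 5.7% are assumed, and 2.5 patients per stratum does not give complete balance. The two harms also trade off, since better balance means a more conservative test but less uncorrected imbalance.

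A reader might also want a baseline-by-visit term. Nothing in the documents shows that its absence matters here.

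Finally, an article condenses the full protocol, and an unseen analysis plan may add covariates. That defence is limited, because the article gives a covariate list that reads as complete. The point rests on what is written.

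**Conclusion.** The point holds as a low-cost improvement. The stated primary model does not match the stratified design. Its standard error is somewhat too large, and precision is forgone, to the extent that the factors predict change beyond the baseline composite. The expected gain from adjusting is about 1 point of power on the document's own figures, and about 3 points if age and site explain a further 6%, which is an assumption.

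Both figures rest on the simulation settings above and on carrying over an R² from unadjusted one-year MMSE change. The share of variance that the factors explain in the 18-month composite, given baseline, is not in the documents and could be smaller or larger.

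**What to change.** In Data Analyses, add age group, glycaemic control and hypoglycaemia-risk drug use as fixed main effects, with the values used at randomisation. Include institution as a random effect, or as a fixed effect with small sites pooled. Apply this to the primary MMRM and to the MMRMs for the secondary continuous outcomes. Fitting all 120 strata is not needed.

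The cost is a line of text and a few degrees of freedom: 3 for the binary factors, and at most 14 more if all 15 sites were fitted as fixed effects, out of roughly 240 evaluable patients. The loss of about 1 to 2 points of power arises only if all sites are fixed effects and no factor is prognostic; a random site effect or pooling limits it. No new data or patients are needed. The change should be made before unblinding, so that the covariates cannot appear to have been chosen on the result.
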